### 2.6. Statistical Analysis

An a priori sample size estimation was performed using G*Power software version 3.1.9.7 [36]. The calculation was based on the primary outcome (CAR), assuming a one-tailed test, a type I error (α) of 0.05, a statistical power (1−β) of 0.80, and a medium expected effect size. Based on these assumptions, the estimated sample size is 102 participants (51 per group).

The data collected will be pseudonymized (a technique that modifies and masks personal and sensitive data of a natural person to prevent direct or easy attribution to the individual) and will be used exclusively for the purposes of the Wear-Smile study project.

Statistical analyses will be performed according to the intention-to-treat (ITT) principle. Per-protocol analyses will additionally be conducted as sensitivity analyses.

The statistical analysis will be applied to analyze continuous and categorical variables, with particular attention to the handling of missing data and the analysis of both intra- and inter-subject variability.

To enhance data interpretation and understanding of distributions, graphical representations such as histograms, boxplots conditioned on the target variable, and scatter plots will be employed.

To minimize the risk of bias due to missing data, a missing data analysis will be performed to assess whether data are Missing Completely at Random (MCAR) or dependent on other variables. If missing data exceeds 5%, it will be handled using multiple imputation techniques based on appropriate statistical models, thereby reducing the risk of bias.

The adoption of these methodologies will strengthen the scientific evidence regarding the effectiveness of telerehabilitation for smoking cessation, optimize result interpretation, and provide valuable insights for future clinical implementations and public health policies.

A sensitivity analysis will be conducted to compare results between the original datasets and the imputed datasets.

Statistical analyses will be performed using SPSS version 28.0, R version 4.2, or STATA version 17.0. The level of statistical significance will be set at *p* < 0.05 for all tests, with Bonferroni correction applied for multiple comparisons to control the risk of Type I error. Effect sizes and 95% confidence intervals (95% CI) will also be reported whenever appropriate.

Before performing inferential analyses, an Exploratory Data Analysis (EDA) will be conducted to describe the characteristics of the sample and to identify any anomalies or patterns in the data.

Continuous variables will be presented as mean and standard deviation (SD) for normally distributed data and as median and interquartile range (IQR) for non-normally distributed data. Categorical variables will be reported as frequencies and percentages. The Shapiro–Wilk test will be used to assess the normality of distributions and determine the appropriate use of parametric or non-parametric tests.

Longitudinal changes in primary and secondary outcomes over time (baseline, 6 months, and 12 months) will additionally be analyzed using mixed-effects regression models accounting for repeated measurements within participants.

Comparisons between the intervention group (telerehabilitation using the integrated telemedicine platform and wearable remote-monitoring devices) and the control group (standard multimodal behavioral-psychological treatment without telemedicine or wearable devices) will be performed using Student’s t-test for normally distributed continuous variables and the Mann–Whitney U test for non-normally distributed variables.

Within-group longitudinal comparisons across follow-up assessments will be performed using paired Student’s t-tests or Wilcoxon signed-rank tests, as appropriate according to data distribution.

Comparisons between categorical variables, including smoking cessation status (abstinent/non-abstinent), will be performed using the Chi-square test or Fisher’s exact test when appropriate.

Associations between the intervention and both primary and secondary outcomes will be explored using Pearson’s correlation coefficient for normally distributed variables and Spearman’s rank correlation coefficient for non-normally distributed variables.

To control for potential confounding factors (e.g., age, gender, comorbidities), multivariate linear regression models will be applied. In addition, multiple logistic regression will be used to identify predictors of successful smoking cessation. The dependent variable will be smoking cessation status (yes/no), and the independent variables will include type of nicotine use (combustible tobacco vs. HTP vs. ENDS), age, gender, motivation, dependence severity, and comorbidities.

Pre-specified subgroup analyses will be performed according to the type of nicotine-containing product used (combustible tobacco cigarettes, heated tobacco products, and electronic nicotine delivery systems), dependence severity, and motivation to quit. In addition, the type of nicotine-containing product will be included as a covariate in multivariable regression models to account for its potential confounding effect on smoking cessation outcomes.

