Participants will be randomly distributed equally (in a 1:1 ratio) into the experimental group (EG) and control group (CG). The random allocation sequence will be carried out by the web-based randomization service Research Randomizer (freely accessible online at: https://www.randomizer.org/, accessed on 26 May 2026) by an independent researcher not involved in participant recruitment, eligibility evaluation, or outcome assessment. Allocation concealment will be ensured using sequentially numbered, opaque, sealed envelopes prepared by the independent researcher. The envelopes will be opened sequentially only after the participant has completed the baseline assessment and has been formally enrolled in the study, thereby preventing foreknowledge of treatment allocation and minimizing selection bias.

Due to the nature of the intervention, participants and healthcare providers cannot be blinded to group allocation. Outcome measures will be collected using standardized assessment procedures to minimize assessment bias by independent researchers not involved in participant recruitment, eligibility evaluation, or randomization allocation.

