### 2.5. Outcomes and Data Collection

#### 2.5.1. Primary Outcome

The primary outcome of the study will be the effectiveness of the program on smoking cessation, assessed through Continuous Abstinence Rates (CARs) and Point Prevalence Abstinence (PPA).

CARs will be defined as sustained smoking abstinence throughout the follow-up period without relapse [28]. CARs will be calculated as the proportion of participants who maintain continuous smoking abstinence at the 6-month and 12-month follow-up assessments without relapse during the observation period.

PPA will be defined as abstinence from smoking at the time of assessment, regardless of any previous smoking relapses during follow-up [28]. PPA will be calculated as the proportion of participants reporting abstinence from smoking at the 6-month and 12-month follow-up assessments, regardless of previous smoking relapses during follow-up.

Both CARs and PPA will be assessed using self-reported smoking status collected through the smoker diary and will be computed 6 and 12 months after baseline [28]. Smoking abstinence outcomes will be assessed through self-reported smoking status, consistent with the telemedicine-based design of the Wear-Smile project.

No biochemical verification of smoking abstinence (e.g., exhaled carbon monoxide or cotinine testing) will be performed.

The timing at 6 and 12 months to assess smoking behavior status was established because a 6-month abstinence period was considered indicative of long-term smoking cessation, as it allows for a more reliable estimation of the proportion of participants who will maintain abstinence even in the subsequent years [8]. A permanent effect of smoking cessation treatment was estimated to be 50% of the Continuous Abstinence Rate at 6 months [8].

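### The 80% power stated for 102 participants rests on a one-tailed, unadjusted 0.05 test, while the described analysis is non-directional with Bonferroni; at a medium effect of h = 0.5 it gives about 70%, less after correction.

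*Protocol article*

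**What the plan says.** All of this is in the protocol article.

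- **Sizing (section 2.6).** "The calculation was based on the primary outcome (CAR), assuming a one-tailed test, a type I error (α) of 0.05". The remaining inputs are "a statistical power (1−β) of 0.80, and a medium expected effect size", and the result is that "the estimated sample size is 102 participants (51 per group"). The software is named as G*Power. The test family, a numeric effect size and abstinence rates are not given.
- **Outcome (section 2.5.1).** CAR is binary: "CARs will be calculated as the proportion of participants who maintain continuous smoking abstinence at the 6-month and 12-month follow-up assessments". PPA is defined at the same two times, and the Abstract lists both among the primary outcomes. That makes four primary comparisons.
- **Analysis (section 2.6).** "Comparisons between categorical variables, including smoking cessation status (abstinent/non-abstinent), will be performed using the Chi-square test" or Fisher's exact test. The significance level is p < 0.05 for all tests, "with Bonferroni correction applied for multiple comparisons to control the risk of Type I error", and 95% confidence intervals are to be reported where appropriate. The number of comparisons in the Bonferroni family is not given.
- **Allocation (section 2.1).** "Participants will be randomly distributed equally (in a 1:1 ratio").

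**The concern.** A sample size supports a power claim only for the test that will be run. Here the sizing spends the whole 5% in one tail and allows for a single comparison. The analysis, as described, uses a 2×2 Chi-square test, which is non-directional, at the same nominal 5%, and then promises a correction for multiplicity. Each change raises the bar for significance, and neither enters the calculation.

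This is the article's only power statement. The word medium also hides how large a gain is needed: at h = 0.5, a rise of 16 to 25 percentage points in continuous abstinence for control rates of 5% to 40%. Section 2.3 says that the behavioural content is the same in both arms and only the delivery differs, so a smaller true gain is plausible. With 80% on record, a non-significant result could be given more weight than it can bear.

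**Working it through.** **Inputs.** From the article: 51 per arm, 1:1 allocation, alpha 0.05 one-tailed, power 0.80, medium effect, Chi-square or Fisher test, Bonferroni. Assumptions: medium means 0.5 (Cohen's d or h); control CAR between 5% and 40%; a Bonferroni divisor of 2 or 4.

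**Step 1: reproduce 102.**

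- Two-sample t-test, d = 0.5, one-tailed 0.05 (noncentral t, df = 2n − 2, noncentrality d·√(n/2)): n = 50 gives 0.799 and n = 51 gives 0.806. The minimum is 51 per arm, or 102. This is an exact match. Two-tailed, the same calculation needs 64 per arm, or 128.
- Two proportions by arcsine, h = 0.5: n = 2(z_α + z_β)²/h². One-tailed: 2(1.645 + 0.842)²/0.25 = 49.5, so 50 per arm. Two-tailed: 2(1.960 + 0.842)²/0.25 = 62.8, so 63 per arm.
- Two proportions by the pooled-variance formula, one-tailed, rate pairs with h = 0.5: 50 to 54 per arm, and 51 for 15% vs 36.4%.
- Chi-square with medium w = 0.3: 88 in total, which does not match.

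**Step 2: the effect implied by h = 0.5.** With p₂ = sin²(arcsin√p₁ + 0.25), the pairs are 5% vs 21%, 10% vs 29%, 20% vs 43%, 30% vs 54% and 40% vs 65%.

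**Step 3: power at 51 per arm, normal approximation.** Here h·√(n/2) = 0.5 × √25.5 = 2.525, and power is Φ(2.525 − z).

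| Test | z | Power |
|---|---|---|
| One-tailed 0.05 | 1.645 | 0.81 |
| Two-sided 0.05 | 1.960 | 0.71 |
| Two-sided 0.05/2 | 2.241 | 0.61 |
| Two-sided 0.05/4 | 2.498 | 0.51 |

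**Step 4: exact power.** Binomial probabilities are summed over all 52 × 52 outcomes, for control CAR 5–40% and h = 0.5.

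| Test | Exact power |
|---|---|
| One-sided 0.05, Chi-square (Fisher if an expected count is below 5) | 0.78–0.82 |
| Two-sided 0.05, same rule | 0.68–0.74 |
| Two-sided 0.05, Fisher throughout | 0.57–0.67 |
| Two-sided 0.05/2, same rule as row 1 | 0.55–0.61 |
| Two-sided 0.05/4, same rule as row 1 | 0.46–0.51 |

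The first row separates the causes. With a binary outcome and a one-sided test, power is still close to 0.80. The drop comes from the second tail and then from Bonferroni.

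**Step 5: what 102 can detect.** At two-sided 0.05, 10% vs 32% has power 0.80 and 20% vs 46% has power 0.81. A 10-point gain has power 0.28 (10% vs 20%) or 0.22 (20% vs 30%).

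**Step 6: sensitivity to the meaning of medium.** If d = 0.5 is converted to an odds ratio, exp(0.5π/√3) = 2.48, and two-sided power by the normal approximation is 0.22–0.62 over the same control rates. If medium meant w = 0.3, it would be 0.86 two-sided and 0.70 with a divisor of four, but w = 0.3 does not reproduce 102.

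**The case against.** The other side has four fair arguments.

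- **A reader might infer that the sponsor sized a binary endpoint with a t-test.** The exact match makes that the likely origin, but the article names no test family. A one-sided two-proportion calculation at 15% vs 36.4% also gives 51 per arm. Nor would the slip explain the loss, since one-sided power for proportions stays at 0.78–0.82. This argument stands.
- **Nothing says two-sided.** Fisher's test can be run one-sided, and sidedness is often left to the analysis plan. This stands only in part. A 2×2 Chi-square is non-directional, the 0.05 level carries no one-sided qualifier, and 95% intervals are promised. A one-sided analysis would not rescue the figure once Bonferroni applies either: at d = 0.5 the one-tailed t-test has power 0.71 with a divisor of two and 0.60 with four.
- **A reader might infer that power simply is 70%, or 50% after correction.** The article supports neither without conditions. Both need h = 0.5, and the lower figure also needs a divisor of four, which is not stated. This stands, so ranges are given.
- **The trial presents itself as preliminary and promises effect sizes with intervals.** That softens the consequence, and misreading of a null result is a risk rather than a certainty. It does not make the 80% correct.

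Missing rates or an attrition allowance may sit in the full protocol and are not held against the article here.

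**Conclusion.** The power statement is wrong as written for the analysis described. Sizing uses one tail and one comparison; the analysis is non-directional and Bonferroni-corrected. This mismatch can be read directly from section 2.6 and is held with high confidence.

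Its size is conditional. With h = 0.5 and control CAR of 5–40%, the stated 80% becomes roughly 70% before any correction. It then falls to between the mid-40s and about 60%, depending on whether two or four comparisons are corrected for. Fisher's test throughout would be lower still.

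Two stronger statements are not supported: that the t-test origin is established, and that the binary outcome itself causes the shortfall.

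**What to change.** Keep 102 and change section 2.6 as follows:

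1. Replace the calculation with a two-proportion calculation for CAR at one named time point (6 or 12 months), stating the assumed control and experimental rates.
2. State the sidedness, and the alpha after whatever Bonferroni divisor the analysis will use, so that sizing and analysis share one test. Name the comparisons in the Bonferroni family.
3. Remove the 80% claim. Report the power that follows at 51 per arm and the smallest detectable difference. At two-sided 0.05 without correction, 80% power needs about 10% vs 32% or 20% vs 46%; a corrected alpha needs a larger gap.
4. Add that a non-significant result does not exclude a smaller worthwhile gain.

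This is wording only. Section 2.7 says that enrolment has not begun, and no extra participants are needed. The cost is that the stated power becomes less favourable. For scale, restoring 80% at d = 0.5 would take 128 participants two-sided, 156 with a divisor of two and 182 with a divisor of four.

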Another relevant strength of the present protocol is the inclusion of persons who smoke different nicotine-containing products, including combustible tobacco, heated tobacco products, and electronic nicotine delivery systems. This aspect may improve the external validity and generalizability of the findings, considering the increasing global diffusion of alternative nicotine delivery products and the ongoing debate regarding their long-term health effects and role within smoking cessation pathways [50].

The present protocol additionally aims to investigate patient-centered outcomes, including usability, treatment acceptability, adherence, and satisfaction with telemedicine-assisted rehabilitation. These aspects are important because two previous umbrella reviews focusing on the use of technology in smoking cessation programs have highlighted a marked lack of data on acceptability and satisfaction [16,51]. Furthermore, low adherence and limited accessibility have been frequently reported as barriers to traditional smoking cessation services [52]. Telemedicine-based interventions may reduce geographical, organizational, and time-related barriers while improving flexibility and continuity of specialist support [53].

Nevertheless, some limitations of the study should be acknowledged. Due to the nature of the intervention, blinding of participants and healthcare providers is not feasible, potentially increasing the risk of performance bias. Smoking abstinence outcomes will primarily rely on self-reported measures, which may introduce reporting bias. In addition, monocentric design may limit the generalizability of the results to different healthcare settings and populations. Potential variability in digital literacy and technological confidence among participants may also influence adherence to wearable device utilization and engagement with telemedicine platforms. Differences in participants’ acceptance of digital health technologies and their long-term engagement with wearable devices may further affect adherence to the intervention and contribute to attrition bias.

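### Missing abstinence status falls under a generic 5% imputation rule, with no specified analysis in which loss may depend on smoking

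*Protocol article*

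**What the plan says.** Section 2.6 of the protocol article sets out one sequence for missing data and does not separate the abstinence outcomes from the rest:

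- A diagnostic step: "a missing data analysis will be performed to assess whether data are Missing Completely at Random (MCAR) or dependent on other variables".
- A handling rule: "If missing data exceeds 5%, it will be handled using multiple imputation techniques based on appropriate statistical models". Nothing is said about 5% or less.
- A check: "A sensitivity analysis will be conducted to compare results between the original datasets and the imputed datasets".
- A general principle: "Statistical analyses will be performed according to the intention-to-treat (ITT) principle". Per-protocol analyses are added as sensitivity analyses.

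Section 2.5.1 defines the two primary outcomes. "CARs will be calculated as the proportion of participants who maintain continuous smoking abstinence at the 6-month and 12-month follow-up assessments"; and "PPA will be calculated as the proportion of participants reporting abstinence from smoking at the 6-month and 12-month follow-up assessments". The source is the participant: "Both CARs and PPA will be assessed using self-reported smoking status collected through the smoker diary". The same section rules out biochemical verification. It does not say how a participant with no report is classified.

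The Discussion (Section 3) says that differences in technology acceptance and long-term engagement "may further affect adherence to the intervention and contribute to attrition bias". It adds that engagement may differ between the arms, and that this will be considered in interpretation and in sensitivity analyses that it does not describe.

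**The concern.** Abstinence is binary and is known only if the participant keeps reporting. Someone who relapses and stops returning the diary is missing because of the outcome itself. Section 2.6 asks whether data are MCAR or depend on other variables. It does not name dependence on the unobserved smoking status, and no test on observed data can detect that.

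The planned comparison of original with imputed results does not fill the gap. The unimputed comparison takes those who stayed in an arm as representative of those who left. Standard multiple imputation does the same, given the predictors in its model. If loss follows relapse in a way the predictors miss, both are off in the same direction and can agree closely.

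At stake are the absolute quit rates and, if informative loss differs between arms, the treatment comparison. The trial compares remote with in-person delivery, so unequal loss is plausible, and the article itself raises the possibility.

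**Working it through.** **Inputs from the article.** There are 102 participants, 51 per arm; the imputation threshold is 5%; abstinence is compared by chi-square or Fisher's exact test. The article gives no quit rate, no dropout rate and no smoking rate among dropouts, so those below are assumptions.

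**Sample size.** A two-sample t calculation with standardised difference 0.5 (an assumed reading of the medium effect), one-sided α 0.05 and power 0.80 gives 51 per arm, total 102, power 0.806. That matches the stated figure with no allowance for dropout.

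**The threshold.** Applied to all 102 participants, 0.05 × 102 = 5.1. Five missing values stay below it and six trigger imputation.

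**Formula.** Let p be the true abstinence rate in an arm, m the share missing and q the share of the missing who are abstinent. A complete-case analysis, or imputation without informative predictors, tends to

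(p − q·m) / (1 − m).

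With q = 0 this is p / (1 − m). With q = p it returns p.

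**Overstatement of one arm's rate** (p = 20%, q = 0):

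- 5% missing: 0.20/0.95 = 21.1%
- 20% missing: 0.20/0.80 = 25.0%
- 30% missing: 0.20/0.70 = 28.6%

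If all five sub-threshold losses fall in one arm and are excluded, 0.20 × 51/46 = 22.2%. At or below the threshold the effect is therefore about 1 to 2 points.

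**Arm contrast with no true effect** (p = 20% in both arms, dropout 15% v 30%):

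| Share of dropouts abstinent | Arm with 15% dropout | Arm with 30% dropout | Spurious difference |
|---|---|---|---|
| 0% | 0.200/0.85 = 23.5% | 0.200/0.70 = 28.6% | 5.0 points |
| 10% | 0.185/0.85 = 21.8% | 0.170/0.70 = 24.3% | 2.5 points |
| 20% | 0.170/0.85 = 20.0% | 0.140/0.70 = 20.0% | 0 |

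The arm that loses more looks better, so the sign reverses if the dropout rates are swapped.

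**Equal dropout with a true effect** (20% v 30%, 20% missing in each arm, q = 0): the estimates are 25.0% v 37.5%. The risk ratio stays at 1.50, and the risk difference goes from 10.0 to 12.5 points. With equal dropout and no true effect there is no bias in the contrast.

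**Type I error.** Simulation with 51 per arm, 200,000 runs, true 20% in both arms, all missing participants smoking, complete-case comparison:

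| Missing, control/experimental | One-sided error | Two-sided error |
|---|---|---|
| 20%/20% | 0.051 | 0.050 |
| 20%/30% | 0.100 | 0.066 |
| 10%/30% | 0.166 | 0.105 |
| 30%/10% | 0.011 | 0.105 |

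Counting missing as smoking gives about 0.05 in every row, as it must when all the missing do smoke. The error rates were computed for complete cases, not for multiple imputation.

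**The reverse case.** If dropout is unrelated to smoking, counting missing as smoking gives 0.20 × 0.85 = 17% v 0.20 × 0.70 = 14%, a spurious 3 points in the other direction.

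**The case against.** The strongest defence is that the article is a condensed document, that the imputation model belongs in the analysis plan, and that multiple imputation is a respectable method. The trial collects daily diary counts, dependence and motivation scores, and device use in the experimental arm. A model that uses them could recover part of the information about relapse, and the formula above then overstates the bias. For CAR, a relapse already recorded in the diary settles the outcome as failure, so some of those who leave are not missing at all. All of this stands. It limits the size of the problem, but a diary that stops also stops supplying predictors.

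Four stronger readings are tempting, and the documents do not support them:

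- *Data are dropped at 5% or less.* The text is silent there. Complete-case analysis is only the likely default, and it would sit badly with the stated ITT principle.
- *Dropouts have mostly relapsed.* Nothing in the article says so. The Discussion links attrition to technology acceptance and engagement, which need not follow relapse.
- *The arm contrast is biased.* That needs informative loss that differs by arm, or a true effect measured as a risk difference or odds ratio.
- *The original-versus-imputed comparison is the only sensitivity analysis.* Per-protocol analyses and unspecified analyses of engagement are also planned. The per-protocol analysis does not address unseen relapse, and the engagement analyses are too vague to count on.

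It is also fair to say that missing counted as smoking is no neutral rule: the last calculation shows it producing a false difference of its own.

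**Conclusion.** The point holds in conditional form. Section 2.6 fixes a handling rule and a check for missing data, and neither suits a self-reported, unverified abstinence outcome. The article does not specify any analysis that lets missingness depend on unseen smoking status, and the check it does specify cannot reveal such dependence. This is a weakness in what the article states, not a detail left to another document.

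Quit rates may be overstated, and the comparison may be biased if informative dropout differs by arm. Under the stated assumptions (20% true abstinence, 15% v 30% dropout, uninformative imputation model) the false difference lies between 0 and 5 points, depending on how many dropouts are abstinent. The material risk is above the 5% threshold; below it, rates move by 1 to 2 points. The change should be made, and Section 2.7 reports that enrolment has not started.

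**What to change.** For CAR and PPA:

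1. Keep all randomised participants in the denominator. Drop the 5% trigger, and do not let the MCAR check decide how missing values are handled.
2. Count any recorded relapse as CAR failure, whether or not the participant is later lost.
3. Pre-specify two analyses: missing counted as smoking, and multiple imputation by arm using diary, dependence and motivation data. Name one of them as primary in advance.
4. Add a tipping-point analysis that varies the odds of smoking among the missing separately in each arm, and report where the conclusion changes.

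The cost is revised wording and a little more analysis. Quoted quit rates will be lower under missing-as-smoking, and that rule can itself bias the contrast if dropout is unrelated to smoking; the tipping-point analysis would show this. Imputation by arm must stay simple: at an assumed 20% abstinence, 51 participants contain about 10 abstainers (0.20 × 51 = 10.2).

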#### 2.5.2. Secondary Outcomes

Secondary outcomes will include the longitudinal assessment of cardiopulmonary parameters, oral health conditions, smoking-related outcomes, health-related quality of life, oral health-related quality of life, and participants’ adherence, usability, acceptability, and patient and healthcare satisfaction with the rehabilitation program.

Cardiopulmonary parameters will include heart rate (beats per minute, bpm), blood pressure (mmHg), respiratory rate (breaths per minute), and oxygen saturation (SpO_2_, %). Heart rate, blood pressure, respiratory rate, and oxygen saturation will be measured twice daily throughout the 12-month study period. In the EG, these parameters will be automatically recorded twice daily through wearable remote-monitoring devices and transmitted to the integrated telemedicine platform. In the CG, the same parameters will be manually self-recorded twice daily using portable medical devices (sphygmomanometers and pulse oximeters) already available in participants’ possession. In addition, in-person clinical cardiology follow-up evaluations will be performed at baseline, 6 months, and 12 months by cardiology specialists for both EG and CG.Oral health outcomes will include probing depth (PD, mm) [29], full-mouth bleeding index (FMBI, percentage of bleeding sites) [30], and full-mouth plaque index (FMPI, percentage of plaque-positive sites) [31]. These clinical periodontal parameters will be assessed by calibrated dental specialists during standardized in-person periodontal examinations at baseline, 6 months, and 12 months. Periodontal examinations will be performed using a manual UNC-15 periodontal probe, and the periodontal parameters will be measured at six sites per tooth.

In addition, self-reported gingival bleeding during toothbrushing will be self-reported twice daily throughout the study period.

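### If the Bonferroni correction is meant to cover the between-arm tests of the secondary outcomes, Holm's procedure gives the same family-wise protection and never rejects less: an optional, modest gain in power

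*Protocol article*

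**What the plan says.** Section 2.6 sets the significance level at 0.05 for all tests, "with Bonferroni correction applied for multiple comparisons to control the risk of Type I error". It does not list the comparisons to be corrected, give their number, or mention the secondary outcomes in this sentence. It also plans effect sizes and 95% confidence intervals, and says nothing of widening the intervals for multiplicity.

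Section 2.5.2 is broad: "Secondary outcomes will include the longitudinal assessment of cardiopulmonary parameters, oral health conditions, smoking-related outcomes, health-related quality of life", followed by oral-health-related quality of life, adherence, usability, acceptability and satisfaction. Most are read at 6 and 12 months. Section 2.6 plans t, Mann-Whitney, chi-square or Fisher tests between the arms, and mixed-effects models over time.

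The sample size of 102 (51 per group) was computed for continuous abstinence alone, "assuming a one-tailed test, a type I error (α) of 0.05", with "a statistical power (1−β) of 0.80" and "a medium expected effect size". It contains no allowance for multiplicity.

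**The concern.** The Introduction makes cardiovascular, respiratory, oral, psychological and quality-of-life effects aims of the study, and the secondary outcomes carry them. With 51 per arm and many tests, a correction that divides 0.05 by the number of tests leaves each outcome with little power. Holm works on the same p-values, needs no further assumption and keeps the same error guarantee. If the secondary tests are to be corrected at all, the choice of method decides whether some real differences are declared, most of all when several related outcomes move together.

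**Working it through.** **1. The plan's own figure.** Reading a medium effect as a standardised difference of 0.5 (an assumption; no number is given), the normal approximation is n per arm = 2(1.645 + 0.842)²/0.5² = 49.5, so 50. The exact one-sided t-test needs 51 per arm (power 80.6%). The stated 102 is reproduced, so 0.5 SD is a fair base case for the secondary outcomes.

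**2. Size of the family (assumed).** Section 2.5.2 names 4 cardiopulmonary, 4 oral, 3 smoking-related and 3 patient-reported measures, 3 scales for usability, acceptability and satisfaction, and adherence: 4 + 4 + 3 + 3 + 3 + 1 = 18. The usability scale rates the telemedicine platform, which controls do not use, so 17 remain. Adherence comes from platform logs in one arm and from visits in the other; without it, 16 remain. Testing 17 measures at two visits gives 2 × 17 = 34 tests. One longitudinal test per outcome would give about half of that.

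**3. Why Holm never does worse.** Bonferroni rejects when p ≤ 0.05/m. Holm orders the p-values and rejects the j-th smallest while p ≤ 0.05/(m − j + 1), stopping at the first failure. Every Holm threshold is at least 0.05/m, so any p-value that passes Bonferroni passes Holm, as do all smaller ones. With m₀ true null hypotheses, the first of them to be rejected meets a threshold of at most 0.05/m₀. The sum over m₀ hypotheses is at most 0.05, whatever the correlation.

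**4. Power under Bonferroni.** Two-sided, 51 per arm: power ≈ Φ(d√(51/2) − z), where z is the normal quantile at 1 − 0.05/(2m).
- d = 0.5, no correction: Φ(2.525 − 1.960) = 0.71.
- d = 0.5, m = 18: Φ(2.525 − 2.991) = 0.32. With m = 17 or 16 it is 0.33.
- d = 0.5, m = 34: Φ(2.525 − 3.180) = 0.26.
- d = 0.6, m = 18: Φ(3.030 − 2.991) = 0.52.

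**5. Power under Holm.** By simulation with 18 tests, 51 per arm and correlation 0.3 between test statistics; average power per truly different outcome:

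| True effects of 18 | 0.5 SD: Bonferroni | 0.5 SD: Holm | 0.6 SD: Bonferroni | 0.6 SD: Holm |
|---|---|---|---|---|
| 1 | 0.32 | 0.32 | 0.52 | 0.52 |
| 4 | 0.32 | 0.33 | – | – |
| 9 | 0.32 | 0.34 | 0.52 | 0.55 |
| 14 | 0.32 | 0.36 | 0.52 | 0.58 |
| 18 | 0.32 | 0.39 | 0.52 | 0.64 |

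With 36 tests, close to the upper count, the figures at 0.5 SD are 0.250 against 0.258 (9 true effects) and 0.251 against 0.268 (18 true effects).

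No replicate had a Bonferroni rejection that Holm missed. In further runs with 4 to 20 tests, the family-wise error under Holm stayed at or below 0.0498. The chance of finding at least one true effect rose by at most 0.2 points, because Holm's first step uses the same 0.05/m.

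**The case against.** The strongest reply is that nothing here is wrong. Bonferroni is valid, conservative and specified in advance, and preferring a slightly sharper valid method comes close to taste. That stands as to severity: there is no false statement, bias or inflated error rate. It does not remove the point, because the method is named in the text and a better one costs a sentence.

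A reader might infer that the protocol ties Bonferroni to the secondary outcomes. It does not: the sentence refers only to multiple comparisons, and could cover the abstinence measures at two visits, the subgroups or the within-group tests. The secondary-outcome family is an assumption here.

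A reader might also infer that power is given away for nothing. That is too strong. Bonferroni has simple simultaneous confidence intervals that match its tests, and Holm has not. The protocol does not use that advantage, since it plans ordinary 95% intervals. More important, the gain is close to zero when few outcomes truly differ. The 12-point gain in the table (0.52 to 0.64) needs all 18 outcomes to differ by 0.6 SD. Sections 2.3 and 2.4 say that counselling content is the same in both arms and only its delivery differs, so effects of that size across so many outcomes are a generous assumption.

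**Conclusion.** The point holds as an optional efficiency gain, on the assumption that the correction covers the between-arm secondary tests. At 0.5 SD with 18 tests, Holm adds about 0, 1, 2, 4 and 7 points of average power for 1, 4, 9, 14 and 18 true effects. At 0.6 SD it adds about 0, 3, 6 and 12 points for 1, 9, 14 and 18. These figures rest on assumed effect sizes, a correlation of 0.3, two-sided tests and an assumed family.

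Most of the loss comes from the size of the family. At 0.5 SD, 18 tests take power from 0.71 to 0.32, and Holm brings it back to 0.39 at best. Holm would therefore not make these outcomes well powered. The primary outcome is not affected. The undefined family is the more practical gap in the same sentence, since neither method can be applied until the number of tests is fixed.

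**What to change.** In section 2.6, replace Bonferroni with Holm's step-down procedure for the between-arm tests of the secondary outcomes, at a family-wise level of 0.05. Name the family: the secondary outcomes measured in both arms, at 6 and 12 months. The platform usability scale then falls outside it, and the text should say whether adherence, which is captured differently in each arm, belongs to it. Report Holm-adjusted p-values with the planned unadjusted 95% confidence intervals.

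The cost is a sentence or two. The named software can do it, and neither the data nor the sample size changes. Section 2.7 says that enrolment has not started, so the change can still be specified in advance. One small downside: an interval may exclude no effect while the adjusted p-value is not significant. The same can already happen with Bonferroni p-values beside ordinary 95% intervals, and a line in the reporting plan can say so.
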